## **8. Analytic Considerations**

### **8.1 Recruitment Sub-study**

We will compare recruitment strategies – email vs. my chart message and ego-centric vs. altruistic messaging – and randomize in a 2x2 fashion. We will make quarterly assessments to compare the four modalities. We will compare response rates between modalities using a binomial test. If it is determined that one modality is better than another, we will drop the weaker modality. The responses will further be analyzed within defined strata. We will use an alpha spending strategy  $p < 0.01$  allowing for a total of 5 comparisons for a total family wise error rate of 0.05.

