## **8.2 Consent Sub-study**

We will compare consent strategy. Again, we will make quarterly assessments. Should one strategy appear weaker than the others, we will discontinue the less effective strategy. We will use the same analytic strategy as above.

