### **2.3 Data Sources**

Potentially eligible patients will be identified using Duke Electronic Health Record (EHR) data, with additional inclusion and exclusion criteria (See protocol section 3.2). No additional data will be used to implement the analyses. Recruitment messages were sent to eligible patients between September 2019 and March 2022.

Invitations to participate in the study will be distributed until the primary study's target sample size meets the requirements set in the protocol (See protocol section 3.1). A REDCap database will be created with the relevant recruitment information and assigned factorial arm. If a participant engages with the invitation's Mytonomy link the responses will be recorded by Mytonomy and delivered to the team in a .csv file upon completion of the study. The consenting information and survey comprehension in the Mytonomy file will be used as endpoints.

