#### 3.4 Multiplicity Adjustments

Multiplicity will be controlled at  $\alpha=0.05$  for the statistical tests associated with the primary objective. A single interim analysis of the primary endpoint was conducted at  $\alpha=0.01$ , leaving the remaining  $\alpha=0.04$  for the final analysis. A global 3 df hypothesis test of any difference between the four consenting strategies will be tested at  $\alpha=0.04$ , and confidence intervals for effect estimates for the primary endpoint (relative risks) will be reported with nominal 96% confidence. Multiplicity will not be controlled between the primary and secondary endpoint analyses, and the secondary endpoint will be tested at  $\alpha=0.05$ , and effect estimates reported with nominal 95% confidence intervals. Subgroup analyses for the primary

endpoint will be considered exploratory, with interactions tested at nominal  $\alpha=0.05$ . All other estimates will be reported with nominal 95% confidence limits.

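### Protocol 8.1 claims a family-wise error of 0.05 from five comparisons at p<0.01, but its own Aim 3 testing schedule does not keep to five

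*Combined protocol and SAP*

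**What the plan says.** Protocol section 8.1 sets the rule for the recruitment sub-study (Aim 3). It names two contrasts, email against MyChart and ego-centric against altruistic content. On timing it says: "We will make quarterly assessments to compare the four modalities". On the test: "We will compare response rates between modalities using a binomial test". On the action: "If it is determined that one modality is better than another, we will drop the weaker modality". It adds analyses within strata, whose number is not given. The threshold is p<0.01, "allowing for a total of 5 comparisons for a total family wise error rate of 0.05". Neither the five comparisons nor a maximum number of looks is given.

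Protocol section 2.2 states three Aim 3 hypotheses: 3a (contact method), 3b (message content, patients with obesity) and 3c (message content, patients without obesity).

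Protocol section 8.2 extends the rule to the four consent formats of Aim 4: "We will use the same analytic strategy as above".

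The Aim 4 SAP departs from that. Its section 3.4 says "A single interim analysis of the primary endpoint was conducted at" 0.01, which leaves 0.04 for a global 3-df final test. The documents contain no SAP for Aim 3.

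**The concern.** A family-wise rate of 0.05 from tests at 0.01 holds only while the count stays at five. Section 8.1 commits to a recurring schedule with more than one comparison per look, so the count grows with time and nothing in the text stops it. The rule has consequences during the trial, because a significant look removes a contact method or a message from use. It also supports the secondary objective of finding the best way to recruit. If the count overruns, a modality may be dropped or declared better at an error rate above the one stated.

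**Working it through.** **Inputs.** Per-test level 0.01, five comparisons, family-wise rate 0.05, quarterly looks and two named contrasts (protocol 8.1); three hypotheses (protocol 2.2). SAP 2.3 says "Recruitment messages were sent to eligible patients between September 2019 and March 2022". That is about 30 months, so at most about 10 quarterly looks. I use it only as an upper bound.

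**Assumptions.** Two-sided tests (8.1 does not state sidedness), equally spaced looks on accumulating data, independent hypotheses, no arm dropped. Independence is reasonable: contact method and content are crossed by randomisation, and 3b and 3c concern separate populations.

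**Step 1: the plan's own figure.** 5 × 0.01 = 0.05, which reproduces exactly. For independent tests, 1 − 0.99^5 = 0.049.

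**Step 2: when the count passes five.**
- Three hypotheses: 3 × 2 looks = 6 tests, so at the second look.
- Two contrasts: 2 × 3 looks = 6 tests, so at the third look.

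**Step 3: error with K looks.** Let q be the chance that one true null hypothesis is rejected at 0.01 at any of K looks. Looks at accumulating data are correlated, so q is below 0.01 × K. I computed q by recursive numerical integration. For m independent hypotheses the family-wise error is 1 − (1 − q)^m. The Bonferroni bound is 0.01 × m × K.

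| Looks K | q (one hypothesis) | Two contrasts | Three hypotheses | Bound, three hypotheses |
|---|---|---|---|---|
| 1 | 0.0100 | 2.0% | 3.0% | 3% |
| 2 | 0.01766 | 3.5% | 5.2% | 6% |
| 3 | 0.02366 | 4.7% | 6.9% | 9% |
| 4 | 0.02858 | 5.6% | 8.3% | 12% |
| 5 | 0.03274 | 6.4% | 9.5% | 15% |
| 10 | 0.04738 | 9.3% | 13.5% | 30% |

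Example, three hypotheses at 4 looks: 1 − (1 − 0.02858)^3 = 0.0833. Simulation agrees to within about 0.1 percentage point. Stratum tests that could trigger a decision would add to every row.

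**Step 4: Aim 4 under the SAP.** 0.01 + 0.04 = 0.05. With a global 3-df test at both analyses, simulated error is 4.3% to 4.8% for interim information fractions of 0.7 down to 0.3. The SAP does not say whether the interim test was global. If it was six pairwise tests at 0.01, the bound is 6 × 0.01 + 0.04 = 0.10, and simulation gives about 7% to 8%.

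**The case against.** The strongest reply is that a total of five comparisons is itself a cap, and five tests at 0.01 do meet 0.05. If the five are looks at a single hypothesis, the error is 3.3%, and one hypothesis stays below 5% even at 10 looks (4.7%). So if 3a, 3b and 3c are separate families, the stated rate holds for each. That arithmetic stands. But section 8.1 claims one total rate for a paragraph that already names two contrasts, and five looks at those two give 6.4%.

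Second, no document says how many looks were planned or made for Aim 3. This also stands. With one interim and a final analysis the excess is trivial (5.2% for three hypotheses) or absent (3.5% for two contrasts). The 10-look figure is an upper bound taken from the invitation window.

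Third, an Aim 3 SAP may exist outside these documents and may have tightened the rule, as the Aim 4 SAP did. That cannot be excluded. Within the documents, section 8.1 is the only multiplicity rule for Aim 3.

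Fourth, Aim 3 is a secondary aim, and section 8.1 does not call its stratum analyses confirmatory. That limits the weight of the point but does not remove the mismatch between the stated rate and the schedule.

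**Conclusion.** The point holds for Aim 3. Section 8.1 states an error rate that its own schedule does not secure, because the five comparisons are neither named nor capped. With 3a to 3c as one family tested at every look, the error passes 5% at the second look, marginally, and reaches 8.3% at 4 looks, 9.5% at 5 and 13.5% at 10. With the two named contrasts it passes 5% at the fourth look. These sizes rest on the assumptions listed in the working and on a number of looks that is not stated.

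A reader might infer two stronger conclusions that the documents do not support.
- That 0.05 is impossible under this rule. It is met if five tests or fewer are done, and for any single hypothesis over as many as 10 looks.
- That the consent comparison carries the same inflation. The SAP reports one mid-study review, after which all four formats were kept. The final global test gave p = 0.07 against a threshold of 0.04, so no difference was declared. Error rates for repeated pairwise looks at four consent arms would describe a scheme the SAP has superseded. What remains for Aim 4 is that protocol 8.2 still carries the old rule and the form of the interim test is not stated.

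**What to change.** **Aim 3.**
- Name 3a, 3b and 3c as the confirmatory tests and divide 0.05 across them, for example 0.05/3 = 0.0167 each.
- Within each share, either use one interim and one final analysis, with one fifth and four fifths of the share as in the Aim 4 SAP (0.0033 and 0.0133; 3 × 0.0167 = 0.05), or use a Lan-DeMets spending function over the looks actually made.
- Label the stratum analyses exploratory.
- Invitations have ended, and a split written now cannot undo a decision already judged at 0.01. So report how many looks and tests were done and the error rate they imply, in place of 0.05.

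**Aim 4.** Align section 8.2 with the SAP (one interim at 0.01, global 3-df final test at 0.04), and state whether the interim was one global test or a set of pairwise tests.

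**Cost.** Wording, a count of the looks taken, and somewhat stricter Aim 3 thresholds. In the two-analysis version the interim threshold falls from 0.01 to 0.0033, while the final one, 0.0133, is slightly looser than 0.01. With a constant threshold over two or more equally spaced looks, it would have to be below 0.01, because two looks at 0.01 already use 0.0177 against a share of 0.0167.

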## **8.2 Consent Sub-study**

We will compare consent strategy. Again, we will make quarterly assessments. Should one strategy appear weaker than the others, we will discontinue the less effective strategy. We will use the same analytic strategy as above.

## **8.3 BCAA Analysis**

### **8.3.1 Sample Size Calculation:**

Based on effect sizes from our previous studies of the BCAA signature of a difference in mean (SD) levels between the two groups of 0.32 (0.95), a sample size of 109 in each group would provide 80% power, indicating that we should have enough power to perform this primary analysis.

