### **2.1. Primary Aims & Hypotheses**

Aim 1: CVD Resistance in Obesity. We aim to understand the clinical, behavioral, and biological factors associated with obesity and CVD risk by understanding differences between obese vs. normal BMI and high vs. low CVD risk groups. To do this, we will develop a cohort of obese and normal BMI patients at high and low CVD risk (n=600), and will deeply phenotype these individuals with behavioral data and biospecimen collection. Half (n=300) will also undergo CT testing to determine coronary artery calcium (CAC) score, for validation of the above associations. Finally, an embedded mechanistic study (n= 40) will explore the effect of the identified markers on vascular endothelial function.

Hypothesis 1a: BCAA are associated with CVD risk in obese individuals more than in normal BMI individuals in a real-world population, and this association will be validated with CAC score.

Hypothesis 1b: Specific clinical, behavioral, metabolomic, genetic, and microbiome profiles will be associated with CVD risk in obese individuals more than in normal BMI individuals.

Hypothesis 1c: In tissue-engineered blood vessels, BCAA interact with lipoproteins to induce endothelial dysfunction and increased monocyte/macrophage accumulation in the arterial wall, which are early markers of atherosclerosis.

Aim 2: CVD and Obesity Resilience. We will implement a proven, digital health behavioral intervention with 400 deeply phenotyped obese individuals in our cohort. We will then explore clinical, behavioral, and biological factors associated with heterogeneity in response to this intervention. Response will be defined as (1) weight loss and (2) changes in CVD risk factors, including LDL-cholesterol, HbA1c, Homeostasis model assessment for insulin resistance (HOMA), and hs-CRP.

Hypothesis 2a: Baseline clinical, behavioral, and/or biological markers, and specifically BCAA, will predict response to the intervention.

Hypothesis 2b: Biological markers, including BCAA and other markers discovered through integrated - omics analysis, will change from baseline with weight loss and changes in CVD risk factors.

Hypothesis 2c: Obese individuals with high CVD risk who lose weight with the intervention will develop biological profiles more similar to normal BMI, low CVD risk individuals.

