### **3. Study Design**

#### **3.1 Overall Study Design**

The RESILIENCE study is a prospective study that will be conducted with 600 patients within the Duke Health System. We aim to recruit patients with 4 phenotypes: 200 patients with obesity (BMI  $\geq 30$ ) and high 10-year ASCVD risk ( $\geq 20\%$ ), 200 patients with obesity (BMI  $\geq 30$ ) and low 10-year ASCVD risk ( $< 7.5\%$ ), 100 patients with normal weight (BMI 18-25) and high 10-year ASCVD risk ( $\geq 20\%$ ), and 100 patients with normal weight (BMI 18-25) and low 10-year ASCVD risk ( $< 7.5\%$ ). We will test recruitment strategies using a 2x2 factorial design that will randomize individuals, stratified by phenotype above, to personal email vs. MyChart message, and to different message content. We will also test consenting strategies by randomizing individuals, again stratified by phenotype above, to 1 of 4 informed consent formats: text only, text + physician video, text + patient video, and text + animated video.

After consent and enrollment, baseline clinical data from the patients' electronic health record will be collected in a database. All patients will be asked to complete a series of behavioral surveys online. They will also be sent a home biospecimen collection kit, with which they will collect and return saliva and stool samples. Once the specimens have been returned, all patients will come for a visit to the Duke South Durham Clinic to have a BMI check and to have fasting labs drawn. At that point, patients with normal weight will exit the study, and patients with obesity will enter into a 6 month weight loss intervention. The intervention, called TRACK, is a proven weight loss program that utilizes health coaching and goal-setting to help patients lose weight. It is a remote intervention that is delivered entirely over their phones. The intervention will be introduced to the participants at the clinic visit, and they will receive a Fitbit and an electronic scale. At the end of the 6 month intervention, the 400 patients will be asked to collect stool specimens again with a home biospecimen kit, fill out additional behavioral surveys online, and have fasting labs drawn.

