#### **3.2 Study Population**

The study population will consist of adult patients who receive care in the Duke Health System, and who fall into 1 of 4 phenotypes: 200 patients with obesity (BMI  $\geq 30$ ) and high 10-year ASCVD risk ( $\geq 20\%$ ), 200 patients with obesity (BMI  $\geq 30$ ) and low 10-year ASCVD risk ( $< 7.5\%$ ), 100 patients with normal weight (BMI 18-25) and high 10-year ASCVD risk ( $\geq 20\%$ ), and 100 patients with normal weight (BMI 18-25) and low 10-year ASCVD risk ( $< 7.5\%$ ). Potentially eligible patients will be identified using Duke EHR data, with the inclusion and exclusion criteria outlined below (see IRB protocol PRO00103647). ASCVD risk over 10 years will be determined using the Pooled Cohorts Equation. For blood pressure and cholesterol (Total Cholesterol & HDL) measures, we will calculate the empirical 1% and 99%

quantiles. Any measures more extreme than these values will be truncated to the 1% and 99% respectively. For those missing any measurements (smoking, cholesterol, etc.), the worst and best case scenarios (based on the 1% and 99%) will be imputed. If a participant's ASCVD risk score is still low risk under the worst case scenario or high risk under the best case scenario, they will be categorized as such. Otherwise they will be excluded from analysis.

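### Protocol 8.3.1 gives 80% power at 109 per group without alpha, sidedness or named groups; the figure reproduces only at one-sided 0.05 (equivalently two-sided 0.10) and does not address the interaction in Hypothesis 1a

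*Combined protocol and SAP*

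**What the plan says.** Section 8.3.1 is the protocol's only power statement for the BCAA analysis. From earlier studies it takes a mean difference of 0.32 with SD 0.95 between two groups that it does not identify, and concludes that "a sample size of 109 in each group would provide 80% power, indicating that we should have enough power to perform this primary analysis". It gives no significance level, sidedness or statistical test. The effect size is credited to reference 13, while the reference list as supplied ends at 12.

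Hypothesis 1a, in section 2.1, is that "BCAA are associated with CVD risk in obese individuals more than in normal BMI individuals in a real-world population". Section 1.2 makes the same comparative claim.

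Sections 3.1 and 3.2 plan four cells: 200 obese high-risk and 200 obese low-risk patients, "100 patients with normal weight (BMI 18-25) and high 10-year ASCVD risk", and 100 of normal weight at low risk. No interaction model, effect size or power is given anywhere. The SAP supplied covers Aim 4 (consent formats) only, so it does not fill the gap.

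**The concern.** There are two separate problems.

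The first is that 80% power has no meaning without an alpha and a sidedness. Most readers would assume two-sided 0.05, and on that assumption 109 per group is too few. The normal-weight cells of 100 are smaller than the stated 109 on any assumption.

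The second is that the calculation concerns one difference between two groups, while Hypothesis 1a says that the high-v-low-risk difference in BCAA is larger in obese than in normal-BMI people. That is a difference between two differences over four cells, and its standard error is larger than that of either simple contrast.

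What is at stake is how the result is read. A non-significant interaction could be taken as evidence against Hypothesis 1a by a reader who believes the study was adequately powered for it. With no test named, the hypothesis might also be judged by comparing p-values between the two BMI strata, where the unequal cell sizes favour a finding in the obese alone.

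**Working it through.** **Inputs.** Difference 0.32 and SD 0.95 (section 8.3.1), so d = 0.32/0.95 = 0.3368. Cells 200/200/100/100 (sections 3.1 and 3.2). Alpha is not stated, so one-sided and two-sided 0.05 are both tried. No dropout is applied at baseline, because section 7.2.3 replaces participants who do not return their initial biospecimens.

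**Step 1: the plan's own figure.** For two equal groups, n per group = 2(z_α + z_β)²/d², with z_β = 0.8416.

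- One-sided 0.05 (the same as two-sided 0.10): 2(1.645 + 0.8416)²/0.3368² = 108.98, so 109. Power at 109 is 80.0% (79.8% by noncentral t). This reproduces the plan.
- Two-sided 0.05: 2(1.960 + 0.8416)²/0.3368² = 138.4, so 139; noncentral t gives 139.3, so 140. Power at 109 is 70.1% (69.7% by noncentral t). This does not reproduce the plan.
- Two-sided 0.04, 0.025 and 0.01 need 148, 168 and 206 per group, so they do not reproduce it either.

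**Step 2: simple contrasts at the planned sizes.** Power for a difference of 0.32:

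| Contrast | Two-sided 0.05 (noncentral t) | One-sided 0.05 (normal approx.) |
|---|---|---|
| Obese, high v low risk, 200 v 200 | 92% | 96% |
| One obese v one normal-weight cell, 200 v 100 | 78% | 87% |
| Normal weight, high v low risk, 100 v 100 | 66% | 77% |
| All obese v all normal weight, 400 v 200 | 97% | 99% |
| All high v all low risk, 300 v 300 | 98% | 99% |

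**Step 3: the interaction in Hypothesis 1a.** Assume SD 0.95 in all four cells.

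- SE = 0.95 × √(1/200 + 1/200 + 1/100 + 1/100) = 0.95 × √0.03 = 0.1645.
- Detectable interaction at 80% power, two-sided 0.05: (1.960 + 0.8416) × 0.1645 = 0.46. One-sided 0.05: (1.645 + 0.8416) × 0.1645 = 0.41.
- Compared with the planning difference: 0.46/0.32 = 1.44.

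The documents give no interaction size, so power can only be shown for assumed values, as Φ(interaction/SE − z_α):

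| Assumed interaction | Two-sided 0.05 | One-sided 0.05 |
|---|---|---|
| 0.32 (for example 0.32 in obese, none in normal weight) | Φ(1.945 − 1.960) = 49% | Φ(1.945 − 1.645) = 62% |
| 0.16 | Φ(0.972 − 1.960) = 16% | Φ(0.972 − 1.645) = 25% |

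If the obese difference is 0.32, any same-direction difference in normal-weight patients makes the interaction smaller and its power lower than in the first row.

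**Step 4: why stratum p-values would mislead.** Suppose the true difference is 0.32 in both strata, so that Hypothesis 1a is false, and each stratum is tested at two-sided 0.05. The chance of significance in the obese alone is 0.919 × (1 − 0.659) = 0.31. The chance of significance in normal weight alone is 0.659 × (1 − 0.919) = 0.05. The imbalance comes entirely from the cell sizes.

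**The case against.** The strongest reply is that nothing in 8.3.1 is shown to be miscalculated. The 109 is correct at one-sided 0.05 or two-sided 0.10. The documents declare no two-sided 0.05 test for BCAA either, and Hypothesis 1a is directional. This stands. A reader might infer an arithmetic error, but the documents support only an undeclared alpha and sidedness.

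The reply continues that 109 is a requirement and not a planned group size, so 70% describes no planned comparison, and that several planned contrasts have ample power. This also stands. A reader might infer that the adequacy statement is false throughout. It is not: it holds for obese high v low risk and for the two pooled contrasts. It does not hold for normal weight, where even one-sided power is 77%.

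A reader might also infer that the primary hypothesis has 49% power. The documents give no interaction size from which to derive that. The 49% assumes an interaction of 0.32 and two-sided 0.05, and it is one point in a range. The detectable effect of 0.46 assumes less, although it still needs SD 0.95 in every cell. That cannot be checked, because the source of the effect size is not in the reference list.

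Finally, a reader might infer that the sponsor intends to test each stratum separately. No passage says so. The synopsis and section 3.1 say only that groups will be compared. Step 4 is therefore a caution about an analysis that the text leaves open, and not a fault in a planned one.

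None of this answers the remaining points: the alpha is missing, the groups are unnamed, and the calculation does not address the interaction.

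**Conclusion.** The point holds. The statement of 80% power at 109 per group is incomplete, and it reproduces only under an alpha that the documents do not declare. Under the conventional two-sided 0.05, which is an assumption here, 109 gives 70% and the requirement is 140 per group (139 by normal approximation). The general claim of enough power fits the obese contrast (92%), falls just short of 80% for 200 v 100 (78%), and does not fit the normal-weight contrast (66%).

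The claim has no support for Hypothesis 1a. Given SD 0.95 in every cell and two-sided 0.05, the interaction would have to be about 0.46, or 1.44 times the planning difference, to be detected with 80% power (0.41 if one-sided). How far actual power falls short depends on an interaction size that the documents do not give.

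**What to change.** In protocol section 8.3.1:

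- State alpha and sidedness, and name the two groups to which the 0.32 (SD 0.95) refers.
- Restate the figures at two-sided 0.05: 140 per group for 80% power; 92% for obese 200 v 200; 66% for normal weight 100 v 100.
- Name the BMI-group by risk-group interaction in a linear model of the BCAA score as the test of Hypothesis 1a, reported with its confidence interval.
- Give its detectable effect, about 0.46 at 80% power, with the assumption of SD 0.95 in all four cells. Quote power at a particular interaction size only if it is labelled as an assumption.
- Limit the statement of enough power to the contrasts it fits.
- State that a stronger association in the obese will not be concluded from one stratum being significant and the other not.

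The cost is a less favourable stated power. No extra patients are needed. The SAP's Data Sources section dates the invitations from September 2019 to March 2022, so the value of the change now lies in how the BCAA results are tested and read.
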